### Data monitoring committee {28}

#### Composition and role {28a}

A formal independent Data Monitoring Committee (DMC) will not be established because the intervention (iron cookware and behaviour change communication) is non-pharmacological, community-based, and considered low-risk. Oversight will instead be provided by the Institutional Ethics Committee (IEC), Government Medical College Akola, Maharashtra, which functions independently from the sponsor and funder and has no conflicts of interest related to the trial. The IEC will review periodic safety and progress reports.

### Interim analyses and stopping guidelines {28b}

No interim efficacy analyses are planned given the modest sample size and limited duration of the trial. However, interim safety monitoring will be undertaken. Serious adverse events (SAEs) and any unexpected safety signals (e.g., severe gastrointestinal events, evidence of iron overload) will be reported immediately to the Principal Investigator and IEC. The IEC retains the authority to recommend protocol modification, temporary suspension, or trial termination in case of safety concerns.

### Trial monitoring {29}

Trial monitoring will be conducted by the study’s internal monitoring team, which will include the Principal Investigator, Co-investigators, and field supervisors. The team will undertake weekly reviews of field logs and enrolment registers, along with monthly household spot checks to verify adherence and data quality. Progress, completeness of data, and safety reporting will be assessed in quarterly project review meetings, while annual reports summarising trial conduct, safety updates, and protocol compliance will be submitted to the Institutional Ethics Committee (IEC). Given the pragmatic and low-risk nature of the intervention, no external contract research organization (CRO) monitoring is planned.

### Research ethics approval {30}

The study protocol has been reviewed and approved by the Institutional Ethics Committee (IEC), Government Medical College Akola, Maharashtra, India. The protocol was reviewed under the Department of Pharmacology and received approval in the IEC meeting held on 25 November 2025. The decision was conveyed on the same date, and the study was assigned IEC Serial No. 123/2025. The approval is valid for the duration of the research, from 01 June 2024 to 31 May 2027. The trial will be conducted in accordance with the principles of the Declaration of Helsinki, Good Clinical Practice (GCP), and applicable national regulations.

### Protocol amendments {31}

Any important modifications to the protocol (e.g., changes to eligibility criteria, outcomes, sample size, or analysis plan) will be submitted for prior approval to the IEC. Approved amendments will also be updated in the trial registry (CTRI/ClinicalTrials.gov) and communicated to the sponsor, investigators, and study team. If required, participants will be re-consented before implementation of changes that directly affect their participation.

### Consent or assent {32}

#### Informed consent/assent process {32a}

Written informed consent will be obtained from all eligible participants prior to enrolment. Trained field investigators, under the supervision of the study investigators, will explain the trial purpose, procedures, potential risks, and benefits in the local language (Marathi/Hindi). Participants will have the opportunity to ask questions before signing or thumb-impressing the consent form.

### Additional consent provisions {32b}

Consent forms will include a section on the collection, storage, and use of biological specimens (blood samples) strictly for trial-related analyses (haemoglobin, ferritin, transferrin indices, CRP). No additional ancillary genetic or biobanking studies are planned. If future use is envisaged, separate consent will be obtained.

### Confidentiality {33}

Personal identifiers (name, address, phone number) will be collected solely for participant follow-up and will be stored separately from study data. Each participant will be assigned a unique study identification code, and only coded data will be used for analysis and dissemination. Paper case report forms (CRFs) will be stored in locked cabinets accessible only to authorized staff, and electronic datasets will be password-protected, encrypted, and stored on secure institutional servers. Data will be retained for at least 5 years after trial completion, after which it will be destroyed in line with institutional policies. The participant flow through the trial is illustrated in Fig. 1 (CONSORT flow diagram).

**Fig. 1 Fig1:**
[figure not shown]
CONSORT flow diagram showing the enrolment, randomization, allocation, follow-up, and analysis of participants in the trial

### Ancillary and post-trial care {34}

At the end of the study, participants will be provided with their iron status reports. Women identified with anaemia will be referred to local primary health centres for free treatment as per the Government of India’s Anaemia Mukt Bharat (AMB) programme. In the event of any research-related harm, appropriate medical management will be provided free of cost, and compensation will be offered as per institutional ethics committee guidelines and national regulations.

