### Criteria for discontinuing or modifying the intervention {15b}

Participants who become pregnant during the trial will be withdrawn from the primary outcome analysis but may be followed up for safety outcomes with consent. Data collected up to pregnancy will be retained for analysis. Participants may discontinue at their own request or if advised by the study physician for medical reasons.

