### Concomitant care permitted/prohibited {15d}

Participants will be asked to avoid initiating iron supplementation or other medications that affect iron metabolism during the trial period, unless medically indicated. Any such use will be recorded, and participants will remain in ITT analyses.

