### Harms {17}

Harms included any adverse event (AE) temporally associated with trial participation/intervention, whether or not considered related, and serious adverse events (SAEs) (death, life-threatening event, inpatient hospitalization/prolongation, significant disability, or important medical events The expected AEs for this trial include minor gastrointestinal symptoms (e.g., nausea, constipation, abdominal discomfort, and dark stools); skin/contact events (e.g., minor burns while cooking); and laboratory abnormalities consistent with changes in iron status. Potential though unlikely safety signals of excess iron will be monitored using ferritin and transferrin saturation (TSAT). The participant timeline, including schedule of enrollment, interventions, and assessments, is shown in Table 2.

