#### Ascertainment and frequency

Harms will be assessed systematically at every study contact (baseline, 3, 6, and 12 months) and during monthly home visits in the intervention period, using a structured checklist and open-ended queries. Participants may also self-report harms at any time via a study phone number/WhatsApp. Field workers will document onset, duration, severity, actions taken, and outcome; supervisors verify within 48 h.

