#### Severity grading and relatedness

Severity will be graded using Common Terminology Criteria for Adverse Events, Version 5.0 (CTCAE v5.0) (Grades 1–5) adapted for community settings [13]. Causality will be assigned by the study physician using WHO-UMC categories (certain, probable/likely, possible, unlikely, conditional/unclassified, unassessable) [14].

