#### Clinical thresholds and actions

If ferritin rises above a pre-specified threshold (e.g., > 150 µg/L in women) and TSAT > 45%, the participant will be reviewed by the study physician; cookware use may be paused and repeat labs obtained. Any burn beyond first-degree or requiring medical care will be recorded as ≥ Grade 2 and treated/referral arranged. Initiation of therapeutic iron by outside providers will be recorded (concomitant care) and monitored for GI AEs [15, 16].

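### Iron status reports are promised only at study end and no low-haemoglobin result triggers action, so a severely anaemic woman could go uninformed for about 12 months or longer

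*Protocol article*

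**What the plan says.** Under Ancillary and post-trial care {34} the protocol article fixes when results are returned: "At the end of the study, participants will be provided with their iron status reports". The next sentence reads "Women identified with anaemia will be referred to local primary health centres for free treatment", under the national anaemia programme. It names no visit and no haemoglobin level.

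Under Clinical thresholds and actions, one laboratory trigger is set: ferritin above a threshold (150 µg/L is the example given) together with transferrin saturation above 45%. In that event "the participant will be reviewed by the study physician; cookware use may be paused and repeat labs obtained". The Harms {17} section likewise names only excess iron as a laboratory safety signal to be monitored.

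Under Concomitant care {15d}: "Participants will be asked to avoid initiating iron supplementation or other medications that affect iron metabolism during the trial period, unless medically indicated". Such use is recorded and the woman stays in the intention-to-treat analysis.

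Haemoglobin is measured at baseline, 3, 6 and 12 months (Data collection {25a}). The eligibility lists set no lower haemoglobin limit, and women anaemic at baseline form a planned subgroup (Additional analyses {27d}).

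**The concern.** The trial recruits where anaemia is common, tests every woman at entry, and asks participants not to start iron unless medically indicated. A woman who has not been told her result has little means of establishing that indication. The expected laboratory abnormality in this population is low haemoglobin, but the only value that prompts a clinical response is the opposite one, which the protocol itself calls unlikely.

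At stake is the safety of any woman who enters with severe anaemia, in either arm. The study team would hold a result calling for treatment while she remains untreated, possibly for her whole follow-up. The two sites' field staff also cannot tell from the text whether to refer at once or at the end.

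**Working it through.** **1. Does any other provision catch a low baseline haemoglobin?**

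| Provision | What it covers | Why it does not clearly close the gap |
|---|---|---|
| Ascertainment and frequency: "Harms will be assessed systematically at every study contact (baseline, 3, 6, and 12 months" | Harms at each contact and at monthly home visits | Anaemia already present at entry is not clearly a harm. The expected laboratory events are "laboratory abnormalities consistent with changes in iron status" |
| Severity grading and relatedness: "Causality will be assigned by the study physician using WHO-UMC categories" | Adverse events | Needs an adverse event first |
| Medical management and compensation | Referral for adverse events | Same |
| Reporting and timelines | Monthly adverse event summaries to an internal safety monitor | Same |
| Discontinuation {15b}: "Participants may discontinue at their own request or if advised by the study physician for medical reasons" | Stopping participation | Presupposes that a physician has seen the result |
| Exclusion criteria (blood count) | Known haematological disorders | No step for a low value |
| Data management {26} (haemoglobin below 5 g/dL) | Implausible data entries | A data query with no clinical action |
| Ethics committee oversight {28a, 28b} | Serious adverse events and unexpected safety signals | Does not address low baseline values |

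None links a low baseline haemoglobin to review, disclosure or treatment.

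**2. Length of the delay**

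- If study end is the woman's own last visit: baseline to 12 months, about 12 months.
- If it is trial completion: December 2025 (recruitment start) to December 2027 (completion), up to about 24 months for the earliest enrolled.

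**3. How many women?** The document gives no figure for severe anaemia, so this is an illustration. Inputs from the protocol: 54–59% anaemic (Study setting {13}), anaemia defined as haemoglobin below 12 g/dL (Table 1), SD 1.2 g/dL and 202 women (Sample size {19}). Assumptions: a normal distribution, an alternative SD of 1.5, and severe anaemia taken as below 8 g/dL.

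Mean = 12 − SD × z(prevalence), with z(0.54) = 0.100 and z(0.59) = 0.228. P(Hb < 8) = Φ((8 − mean)/SD).

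| SD | Prevalence | Mean | P(Hb < 8) | Expected of 202 | P(at least one) |
|---|---|---|---|---|---|
| 1.2 | 54% | 11.88 | 0.00061 | 0.12 | 12% |
| 1.2 | 59% | 11.73 | 0.00095 | 0.19 | 17% |
| 1.5 | 54% | 11.85 | 0.00514 | 1.04 | 65% |
| 1.5 | 59% | 11.66 | 0.00736 | 1.49 | 78% |

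The last column is 1 − (1 − p)^202. Below 7 g/dL the largest probability is 0.00095, or 0.19 women. The result depends strongly on the SD: at 1.8 the expected number below 8 g/dL would be 3.4 to 4.7.

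**4. What would acting on low values cost in power?**

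The plan's own figure reproduces: 2 × (1.2 × (1.960 + 0.842)/0.5)² = 90.4 per arm; 90.4/0.9 = 100.5, rounded up to 101 per arm, 202 in total.

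After 10% attrition, n = 202 × 0.9/2 = 90.9 per arm. In the worst case each referred woman contributes no treatment effect, so the difference becomes 0.5 × (1 − share referred). Two-sample t test, SD 1.2, two-sided 5%:

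| Share referred | Difference (g/dL) | Power |
|---|---|---|
| 0% | 0.500 | 79.8% |
| 0.75% | 0.496 | 79.2% |
| 1% | 0.495 | 79.0% |
| 3% | 0.485 | 77.3% |
| 54% (all anaemic women) | 0.230 | 25.1% |
| 59% (all anaemic women) | 0.205 | 20.9% |

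The 0.75% row is about the largest share in step 3; the 1% and 3% rows are assumptions.

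For ferritin, the primary outcome in Table 1, the document gives no SD or target difference. As an illustration only, assume the same standardised effect as haemoglobin (0.5/1.2 = 0.417) and that iron treatment shifts a treated woman's ferritin by S standard deviations in either arm. With a share q referred, the effect is multiplied by (1 − q) and the SD by √(1 + q(1 − q)S²). For S between 0 and 3, power is 76–79% at q = 1% and 67–77% at q = 3%.

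**The case against.** The strongest reply is that the text need not be read as withholding anything. It says when reports are provided; the referral sentence, which is what delivers care, carries no end-of-study condition. The section is headed ancillary as well as post-trial, and its sentence on research-related harm plainly applies during the trial. Referral on identification is therefore a fair reading, and it fits the allowance for medically indicated iron. This stands as an ambiguity: on that reading most of the delay in care disappears. It does not alter the stated timing of reports, and a safety step should not depend on which reading field staff choose.

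Second, alert values and disclosure terms often sit in procedures or consent forms, which are not shown and may add such terms. That is fair for routing detail. But the article itself fixes the report timing and prints a list of clinical thresholds with nothing on the low side.

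Third, that list belongs to the harms section, where a threshold for excess iron is appropriate, and a fall in haemoglobin during follow-up could plausibly be captured as an adverse event. Both points are right. They narrow the gap to a low value already present at baseline.

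Fourth, at the protocol's own SD of 1.2 the affected group may well be empty. This also stands, and the higher counts and the 24-month delay depend on assumptions or on a less favourable reading.

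**Conclusion.** The concern holds, as a patient-safety point that should be fixed. Reports are timed to study end, referral is undated, and the only laboratory trigger for physician review is for excess iron. On the study-end reading, a severely low baseline haemoglobin may go undisclosed for about 12 months, and for up to about 24 in the earliest enrolled if study end means trial completion.

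The number affected cannot be derived from the document and is probably small: 0.1–1.5 of 202 women, with a 12–78% chance of at least one, under the assumed normal distribution, SDs of 1.2 and 1.5, and an 8 g/dL cut-off. The conclusion rests on the consequence for an individual woman, not on the count. Confidence is medium, because the referral sentence can also be read as applying at any visit and the consent form is not shown. The sample size is not in question here.

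**What to change.** - In Clinical thresholds and actions, add a low-haemoglobin action level for severe anaemia, set by the investigators and the ethics committee. It should apply in both arms and at every visit, including baseline. The study physician reviews the result when it is issued, and the woman is told and referred at once.
- In Ancillary and post-trial care, state that reporting and referral at that level do not wait for study end, and say when other anaemic women are referred.
- Route low values, including those flagged by the data range check, to the physician through the Principal Investigator, who already holds the linkage file. Laboratory staff and statisticians then stay blinded.
- Record any iron started as concomitant care and keep the woman in the intention-to-treat analysis, as the protocol already provides.

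The cost is protocol and consent wording plus physician review of results already produced. The worst-case loss of haemoglobin power is under 1 percentage point at the modelled shares and about 1–3 points if 1–3% are referred. The loss for ferritin is uncertain and could be larger, as the illustration shows. The trigger should be based on severity: referring every woman below 12 g/dL for treatment could, in the same worst case, cut haemoglobin power to about 21–25%. The timing chosen for less severe anaemia should be weighed against that.

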## Discussion

The study will assess improvements in iron status indicators haemoglobin, serum ferritin, transferrin saturation, and total iron-binding capacity among women consuming food cooked in iron pots. It will evaluate compliance and identify cultural, economic, and practical barriers to sustained use. Beyond clinical outcomes, the study aims to establish iron cookware as a cost-effective, scalable strategy to combat iron deficiency anemia in India. Findings will inform public health policies through scientific evidence, policy briefs, and community education tools, supporting its integration into “Anaemia Mukta Bharat” programs. Key deliverables include publications, policy recommendations, and training materials for community health workers [12, 19].

Our study has a number of important strengths. By testing the use of iron cookware alongside behaviour change communication, we explore a simple, low-cost and culturally acceptable approach that could be integrated into everyday cooking practices in rural households. Unlike many previous programs that focus mainly on pregnant or lactating women, we deliberately chose to include non-pregnant, non-lactating women, who also carry a high burden of anaemia but are often neglected in public health interventions [20]. The trial follows a rigorous randomized design, with clear adherence to the SPIRIT 2025 guidelines, and collects a wide range of outcomes from blood markers such as haemoglobin and ferritin to detailed dietary information and qualitative insights on compliance [21]. Because the intervention is delivered through community and primary health settings, its results may be directly useful for policy and program scale-up [3]. At the same time, there are limitations. As cookware use cannot be blinded, participants know which group they belong to, and this could influence their behaviour [19]. Dietary recalls and self-reported compliance may not always be accurate, despite efforts to validate them. Finally, the trial is confined to rural blocks of Maharashtra and follows women for only 12 months, so its findings may not fully apply to other settings or reflect longer-term sustainability [22].

This study anticipates generating new knowledge on the effectiveness of iron cookware in improving iron status across diverse demographic groups in Indian households. By evaluating changes in hemoglobin and iron biomarkers, it will provide evidence on the bioavailability of iron leached during cooking [9]. The research will also identify compliance rates, user acceptability, and practical barriers, offering insights into cultural and behavioural factors influencing cookware adoption. Additionally, the findings will contribute to public health strategies by comparing the intervention with existing anemia prevention measures, ultimately providing actionable recommendations for addressing iron deficiency anemia in resource-limited settings [8, 9].

### Trial status

Protocol version: 1.0, dated May 2025Recruitment starts: December 2025Expected completion: December 2027

## Data Availability

The datasets generated and analyzed during the current study are not publicly available due to participant confidentiality and privacy protections but are available from the corresponding author upon reasonable request.

## Abbreviations

IDA: Iron deficiency anemia
RCT: Randomized controlled trial
BCC: Behavior change communication
Hb: Hemoglobin
TSAT: Transferrin saturation
TIBC: Total iron binding capacity
MCV: Mean corpuscular volume
CRP: C-reactive protein
NPNL: Non-pregnant, non-lactating
NFHS: National Family Health Survey
IEC: Institutional Ethics Committee
FGD: Focus group discussion
